#### 3.5.2 Informed consent, baseline assessment and randomization (T0).

Before starting the baseline assessment, participants will be given enough time to request more trial details and to decide whether they wish to participate. Participants will be required to sign the informed consent form.

After signing the informed consent all participants will undergo a full blinded baseline assessment that consist of the following:

Past medical history, including characteristics of AAA (diameter and location), current medication, ASA status [73], Charlson Comorbidity Index [74], and CSHA Clinical Frailty Scale [75].Resting blood pressure, heart rate and oxygen saturation.Participant demographics: age, sex, gender, and education level.Body composition: height, weight, body mass index, Fat-Free Mass (kg), fat mass. Nutritional status will be assessed using the Patient Generated Subjective Global Assessment (PG-SGA).6-Minute Walk Test, which will assess functional capacity in relation to activities of daily living). The 6MWT will be executed following the American Thoracic Society guidelines for the 6MWT [62].Cardiopulmonary exercise test (CPET) conducted by an exercise physiologist/kinesiologist/physiotherapist with expertise in comorbid population under the supervision of a physician. Reliability and safety of CPET in participants with AAA have been previously demonstrated [26,36,51]. CPET will be performed following the iPOETSS - International Prehabilitation and Exercise Testing and Training Society guidelines in all centers [76]. The data obtained during CPET (physiological variables in response to exercise and workload in watts at the anaerobic threshold and at peak/maximum exercise) will be used in the intervention group to tailor the intensity at which the participants will perform the aerobic exercise prescription. If a non-previously diagnosed pathology that poses a threat to the health of the participant (such as an exercise contraindications as listed in the exclusion criteria) is detected with the CPET, the patient will be excluded from the study and will be referred to the appropriate health care resource.Physical activity measured with the Yale Physical Activity Survey (YPAS).Health-Related Quality of life using the Medical Outcomes Study SF-36 V.2 questionnaire. This quality-of-life questionnaires has been previously used in this population.Anxiety and Depression measured using the Hospital and Anxiety scale (HADS).

***Randomization*:** Randomization will be performed after baseline assessment. Participants will be randomized to both arms equally a (1:1 ratio) upon final confirmation of eligibility. A stratified randomization will be performed by site and sex; with block size 2,4 and 6 to ensure unbiased allocation of the patients. Allocation to study group will be revealed using RedCap software to the research team that will carry out the intervention once baseline assessment is completed.

#### 3.5.3 Standard of care (T1-T6).

Participants in the control group will receive the standard of care according to each center’s practice. This will include comorbidity optimization with special emphasis on blood pressure management according to international hypertension guidelines, anemia correction and smoking cessation advice if deemed appropriate [77,78].

#### 3.5.4 Multimodal Prehabilitation program (MP) (T1-T6).

Participants in the intervention group will undergo, in addition to the standard of care, 6 ± 1 weeks of a personalized multimodal prehabilitation program. The interventions included will be patient-centered, aiming to optimize patients’ preoperative health status while enhancing their empowerment and engagement. The main components of the program will consist in:

**i. Supervised exercise program**: This will entail two 1-hour supervised sessions per week of aerobic and strength training, with at least one day of rest in-between. During the first session, an exercise specialist (kinesiologist, sport physician or physiotherapist) will assess participants’ mobility and capacity to undertake exercise. As previously mentioned, the exercise intensity for the endurance training will be defined and personalized based on the individual CPET values obtained during baseline assessment. The exercise specialist will also assess the maximum tolerated weight for each big muscle group using the eight-repetition maximum test that will allow to establish the initial weight for the strength training. Based on the evaluation, a personalized program from the protocolized program will be generated, as defined in S2 File. The supervised session will be carried out in a supervised setting (hospital or community-based facility). Heart rate, blood pressure, oxygen saturation (if lung disease present) and perceived exertion rate using the modified Borg scale (for both breathing and muscle fatigue) will be monitored throughout the training session. After each session of supervised exercise participant will receive 0.4g·kg of whey protein supplementation to promote anabolism unless contraindicated due to milk allergy or galactosemia in which case a soy-based protein will be provided [79].**Supervised aerobic training** will consist of ~45 min of HIIT on a stationary bicycle. Each aerobic session will typically include 10 minutes of warm-up and 5 minutes of cool-down pedaling at 30%–40% of their peak workload attained during CPET. An interval training will consist in at least 5 bouts combining 2 min of high-intensity exercise. The high intensity bouts will start at 70% of peak workload and will be progressed in 5% weekly increases up to 90%–100%, although progression will be tailored on individual basis to ensure tolerance, safety and maximize the training. The high intensity bouts will be interspersed with 3 min recovery periods at lower intensity (40%–50% of the peak workload). Blood pressure, heart rate, SpO2, leg fatigue Rate of Perceived Effort (RPE-L) and breathing RPE (RPE-B) will be monitored throughout the session during high intensity bouts and during the recovery periods. A stepwise reduction of workload by 10% will be deemed pertinent if participant cannot tolerate the workload during peaks or if systolic blood pressure rises >180 mmHg or HR rises >95% of maximal HR attained during CPET. If HIIT is not well tolerated by the participant despite the progressive reduction of workload (repeated BP > 180 mmHg/ HR > 95% or other exercise intolerance during high intensity), an alternative exercise prescription will be proposed, consisting in moderate intensity continuous exercise (40–60% of peak workload or RPE 4–6/10).**Supervised strength training** will consist of 2–3 upper (pectoralis and latissimus dorsi) and lower (quadriceps) limb exercises based on 2–3 sets of 8–12 repetitions always avoiding Valsalva’s maneuvers. The initial weight will be based on 60–70% of the eight-repetition maximum test. The weight and/or the number of repetitions will increase every week, if tolerated by the participant, to ensure strength progression and maximize the training effect. The weight and/or the number of repetitions will be decreased if systolic blood pressure rises >180mmHg or HR rises >95% of maximal HR.**ii. Home-based training and promotion of physical activity**:

During the first session, the exercise physiologist/kinesiologist/physiotherapist will use motivational interviewing techniques to promote physical activity and healthy lifestyle. The motivational interview will focus on empathy, reflective listening, and affirmation, and will address the participants’ barriers and limitations related to physical activity. The role and safety of exercise and physical activity during the preoperative period will be discussed and participants will be taught on how to perform exercise on their own within the safety limits. Participants will follow a home-based exercise program containing aerobic, strength, and inspiratory muscle training (IMT) exercises. Participants will receive a logbook where the exercise specialist will prescribe the intensity, type, time, and frequency of aerobic, strength and IMT exercises. Each time the participant performs the prescribed home-based exercises they will register their activity in the logbook provided, including the RPE at which they trained. The exercise specialist will review the logbook every week and will adjust the home-based exercise plan accordingly to ensure both safety and exercise progression. Furthermore, all participants will receive a pedometer at the beginning of the 6-week period that will allow tracking of daily physical activity in both groups.

**Aerobic exercises:** participants will be instructed on how to conduct aerobic exercises at home in a low-moderate intensity, by either walking or cycling initially at RPE 2–4/10 for 20 min at least once per week. This will be increased in stepwise increments by 10% each week if tolerated.**Inspiratory muscle training:** daily IMT with an inspiratory threshold-loading device (threshold IMT) will be prescribed. During the first visit with the exercise specialist the maximal inspiratory mouth pressure will be measured, and participants will be taught to perform daily IMT exercises at 30% of their maximal inspiratory mouth pressure. The pressure will be increased by 5% each week if the rate of perceived exertion scored on the Borg scale is < 5/10.**Strength exercises:** participants will be instructed to conduct low intensity whole-body muscular strength exercises at home using an elastic band at least one time per week. The exercises will be adapted to each individual’s capacity and could include 2–3 sets of 8 repetitions of wall push-ups, sit-ups, calf raises, hamstring kickbacks, or standing strides (lunges). Progression of the exercises will be made by increasing the number of repetitions up to 12, or by changing the exercise if deemed appropriate.

**iii. Nutritional assessment, education, and supplementation**

To enhance the anabolic effect of physical training, improve fat free mass and obtain or maintain an optimal nutritional status during the preoperative period, sufficient intake of energy nutrients (especially protein) is required [80]. Participants will meet with a registered dietitian for one initial session and at least one follow-up session. This session will include the following:

**Assessment:** the dietician will assess the participant’s nutritional status using the parameters measured during baseline assessment (PG-SGA, body weight, height, Fat free mass, and body fat). Moreover, the participant will be asked to fill in a three-day food diary or conduct a 24h-recall prior to their meeting with the dietician, which will be used to estimate habitual macronutrient consumption.**Education:** learning correct portion sizes, improving diet quality by building a balanced plate and reducing ultra-processed foods, adequate fiber intake through whole grains, vegetables and legumes, learning sources and importance of protein, importance of timing and spacing of meals, encouraging food sources of amoga-3 fatty acids, along with practicing mindful eating. Promotion and encouragement of dietary changes to ensure balanced intake with adequate protein, weight management, and the regulation of blood glucose will be discussed. Possible barriers to attain the proposed dietary changes and ways to overcome them will also be discussed along with the importance of perioperative nutrition, using a COM-B questionnaire. Based on estimated habitual protein intake, participants will receive a tailored dietary advice aiming to meet a total protein intake of 1,2–1,5g/kg daily (ideal body weight if BMI > 30), unless contraindicated and 20–30 Kcal/kg daily (20 Kcal/kg for weight loss, 25 Kcal/kg for maintenance and 30 Kcal/kg for gain). [80]. Participants will be instructed to evenly ‘spread’ their protein intake over 3 meals with a minimum of 25–30 gram of protein/ meal.**Supplementation:** To stimulate muscle protein synthesis, participants will also be provided with 0,4g/kg (adjusted to ideal weight if BMI > 24.9) of whey protein powder immediately after supervised strength training (2 times a week). Micronutrient deficiencies, including vitamin D will be assessed by the dietician, who will recommend their supplementation as needed.

**iv. Psychosocial intervention**

It is expected that patients undergoing surgery feel some degree of anxiety and depression. Since both anxiety and depression can influence the motivation to carry out social and functional activities as well as partaking in the prehabilitation program, psychological strategies can be put in place to help patients to cope with the stress of surgery and disease. Therefore, participants will receive one hourly session of psychological intervention called “surgical stress tolerance training”. In this session the psychosocial specialist will address the patient’s anxieties, coping strategies, and post-operative expectations, with the goal of optimizing psychological well-being & ways of coping with surgery. The importance of the patient’s active participation in the preparation for surgery and healing process will also be discussed. All participants in the intervention group will be given instructions on relaxation and deep breathing techniques that they can practice at home with a guided relaxation audio that will be provided via CD or USB key. A follow-up session during the prehabilitation period will be offered to those participants who score high in anxiety and depression in the HADS questionnaire (8 points or more) or those participants who request an additional session.

#### 3.5.5 Preoperative assessment (T7).

Six weeks after the baseline assessment, or the week prior to surgery if surgery happens >6 weeks after baseline, participants will undergo a preoperative assessment with the same measurements performed at baseline assessment (resting blood pressure, heart rate oxygen saturation, body composition, PG-SGA, 6-Minute Walk Test, CPET, YPAS, SF-36, HADS questionnaire). Participants will be offered the possibility to continue training until their week of surgery; in case it gets delayed. In addition to these measurements, the intervention group will be invited to fill out a satisfaction survey regarding the different components of the prehabilitation group that can be found in the S1 File.

#### 3.5.6 Surgery and admission (T8).

Perioperative clinical protocols will be followed according to each site’s standard of practice independently of group allocation; [76]. Anesthesia procedures and surgery will be performed by the usual anesthesia and vascular surgery teams of each site. Hospital healthcare providers (nurses, anesthesiologist, vascular surgeons, physiotherapists, etc.) involved in the participants care will be blinded to the study group allocation, unless the participant discloses that information. To avoid that, participants will be advised not to disclose their allocation to healthcare providers. Any intraoperative deviation of the standard course or event will be recorded (S3 File). The use of blood products, as well as the need for high doses of vasopressors intraoperatively will also be recorded (high doses of one vasopressor or the use of two or more vasopressors) in the case report form. Postoperative care will not differ between groups and will follow the standard of practice for each site. Postoperative complications throughout admission will be assessed daily by a physician and will be recorded in the CRF by a research team member. Both team members will be blinded to the study group allocation to avoid bias. The primary outcome of the study, the Comprehensive Complication Index (CCI), will be calculated based on the number and severity of the complications recorded. A description of complications and their severity can be found in the S4 File. Length of ICU stay, need for a reintervention and hospital length of stay will be recorded.

#### 3.5.7 Postoperative assessment (T9).

Six weeks after discharge, participants will undergo a postoperative assessment where the following measurements will be performed:

Resting blood pressure, heart rate and oxygen saturation.6-Minute Walk TestYale Physical Activity SurveySF-36 V.2 questionnaireHADs questionnaire

Emergency room visits and readmissions, from discharge to postoperative assessment, will also be assessed and recorded.

#### 3.5.8 1-year follow-up (T10).

One year after discharge participants will be contacted by a research team member via phone call to enquire about admissions to ER visits and hospital admissions. Hospital records will be also assessed to track any ER visits, hospital admissions and mortality. A package of questionnaires will be sent via postal mail or email which will include SF-36, HADs and YPAS.

### 3.6 Statistical analyses

#### 3.6.1 Sample size.

Sample size was calculated for the primary outcome of complications as defined by the CCI. From the literature, the mean CCI ranges from 25–35 after open AAA repair, and their standard deviations are 17–30. We have chosen 30 as the most clinically relevant mean difference for the CCI and standard deviation of 20. Given the inputs, we require a total of 126 patients to achieve standard 80% statistical power and 5% tolerance. After considering a 20% dropout rate, we require 152 patients (76 per group) in this study. Since one interim analysis was planned, a total of 40 patients were needed in each treatment arm at the time of analysis to adequately power the interim analysis based on the type-I error suggested by the O’Brien-Fleming method (a minimum P = 0.0054).

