## 3. Methods and analysis

### 3.1 Trial design and ethics

The trial protocol was written following the Standard Protocol Items: Recommendations for Interventional Trials (SPIRIT) guidelines [54]. This is a prospective, international, multicenter, open label, randomized controlled trial with an allocation ratio 1:1 comparing standard of care versus 6 weeks of a multimodal prehabilitation program. The recruitment period started in September 2024 and will last until September 2027. Recruitment of participants will take approximately three years, the follow-up and data collection after recruitment phase will last one year, and results will be analysed within a year of finishing. Both primary endpoint and baseline data will be blindly assessed. Intention-to-treat criteria will be used to define the analysis population; all randomized participants will be included in the analysis according to assigned group. The trial is registered on the Registry of National Institutes of Health ClinicalTrials.gov, a database of privately and publicly funded clinical studies conducted around the world (NCT05756283). The trial will be conducted according to the rules of Good Clinical Practice. The study will be conducted according to the principles of the Declaration of Helsinki and in accordance with the Medical Research Involving Human Subjects Act (WMO) and has been reviewed by the ethics board of McGill University Health Centre MP-37-2023-8983. No datasets were generated or analysed during the current study. All relevant data from this study will be made available upon study completion.

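### The stated 30-point CCI difference does not give 126 patients; that number fits a difference of 10 points, so the key design figure is wrong by a factor of three

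*Protocol article*

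**What the plan says.** Section 3.6.1 of the protocol article sizes the trial on the Comprehensive Complication Index (CCI), compared between two arms allocated 1:1 (section 3.1). It gives the background range as "the mean CCI ranges from 25–35 after open AAA repair, and their standard deviations are 17–30". It then fixes the planning values: "We have chosen 30 as the most clinically relevant mean difference for the CCI and standard deviation of 20". The next sentence presents the number of patients as their consequence: "Given the inputs, we require a total of 126 patients to achieve standard 80% statistical power and 5% tolerance". The inflated figure follows: "After considering a 20% dropout rate, we require 152 patients (76 per group) in this study".

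No other section gives a target difference, and a difference of 10 points appears nowhere in the article. Whether the 5% is one- or two-sided is not stated.

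**The concern.** The two consecutive sentences cannot both be right. A difference of 30 with SD 20 is a standardised effect of 1.5, which needs a handful of patients per arm. A trial of 63 per arm is sized for a standardised effect of about 0.5.

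The 30 is also hard to believe as a difference. Section 3.4.1 defines the CCI from 0 (no complications) to 100 (death). With a control mean of 25–35, a 30-point reduction would bring the prehabilitation arm to between 0 and 5, or below the bottom of the scale if the control mean were 25. Since 30 is the midpoint of 25–35, it looks like the assumed control mean put in the place of the difference.

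This is the only place where the trial says what effect it is designed to detect and regards as clinically relevant. As printed, a benefit of 10 to 15 points would fall short of the trial's own figure, although about 10 points is what its size is suited to detect. The 80% power would also refer to an effect that the design does not use. Ethics boards, the DSMB and later readers cannot tell from the text what the trial can detect.

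**Working it through.** **Inputs**

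- Difference 30, SD 20, 80% power, 5% error: section 3.6.1.
- Allocation 1:1: section 3.1.
- Literature range for the SD, 17–30: section 3.6.1.
- Assumption: two-sided test. One-sided is also tried, because the text does not say.

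**Formula.** Comparison of two independent means, normal approximation:

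n per arm = 2 × (z₁₋α/₂ + z₁₋β)² × (SD/difference)², with (1.960 + 0.8416)² = 7.849.

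**1. The plan's own inputs**

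| Difference | SD | Test | n per arm | Total |
|---|---|---|---|---|
| 30 | 20 | two-sided | 2 × 7.849 × 0.4444 = 6.98, so 7 | 14 |
| 30 | 20 | two-sided, t-test | 8.06, so 9 | 18 |
| 30 | 20 | one-sided | 6 | 12 |
| 30 | 30 | two-sided | 15.7, so 16 | 32 |
| 30 | 30 | two-sided, 90% power | 22 | 44 |

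None of these is near 126. Lowering alpha slightly for the interim look (0.0492 or 0.048) gives 16 in total at SD 20.

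**2. What would produce 126 (63 per arm)**

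- Keep the difference at 30 and solve for the SD: 30 / (2.8016 × √(2/63)) = 60.1, twice the top of the quoted range.
- Keep SD 20 and solve for the difference: 2.8016 × 20 × √(2/63) = 9.98 points.
- Forward check with 10 points and SD 20: 2 × 7.849 × 4 = 62.79, so 63 per arm and 126 in total, an exact match. The t-test gives 64 per arm, 128 in total.

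**3. Other readings of the 30**

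- 10 points, one-sided: 100 in total.
- A 30% relative reduction from a mean of 30 (9 points): 156 two-sided, 124 one-sided.
- A 30% relative reduction from 25 (7.5 points) or from 35 (10.5 points), two-sided: 224 or 114.

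Only the one-sided 9-point reading comes close to 126. Under it, a printed difference of 30 is still wrong by 30/9, about threefold.

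**4. Power at 63 per arm, two-sided 5%**

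Power ≈ Φ(difference / (SD × √(2/63)) − 1.960), with the noncentral t value alongside.

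| Difference | SD | Normal | Noncentral t |
|---|---|---|---|
| 30 | 20 | >99.99% | >99.99% |
| 10 | 17 | 91.0% | 90.6% |
| 10 | 20 | 80.1% | 79.5% |
| 10 | 25 | 61.2% | 60.6% |
| 10 | 30 | 46.4% | 45.9% |

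**The case against.** The arithmetic is not in dispute. The case against concerns what is built on it.

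- **The 10 points is inferred.** The article never states it, and the sidedness is open. That is fair: 10 is a back-calculation, and that 30 is a misplaced control mean is a plausible guess. But 10 points with SD 20, two-sided, reproduces 126 exactly, and the one near alternative leaves the printed 30 just as wrong.
- **The interim statement does not fit 10 points.** Section 3.6.1 says "a total of 40 patients were needed in each treatment arm at the time of analysis" to power the interim look at P = 0.0054. For 10 points, SD 20 and 40 per arm, power there is Φ(10/(20 × √(2/40)) − 2.782) = Φ(2.236 − 2.782), about 29% (27% by the t-test). This is a separate problem, and it does not rescue 30: at that level a 30-point difference needs 24 patients in total and a 10-point difference 212, so 80 follows from neither.
- **A planning value is not a success criterion.** Correct. Sections 3.6.2 and 3.6.3 set no rule based on 30, so the analysis is unaffected. The damage is to what the trial says it can detect and to how its result will be read.
- **No added patients is not guaranteed.** Partly right. With 152 randomised and 20% lost, about 61 per arm remain (0.8 × 76 = 60.8), giving 78–79% power for 10 points. That comes from the dropout inflation, a separate question from the misstated difference.

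**Conclusion.** The concern holds. The stated inputs give 14 to 18 patients in total, not 126, and no standard variant with a 30-point difference comes near 126. With the stated SD of 20 and a two-sided 5% test, 126 corresponds to 10 points, so the printed target is three times the effect that the trial is sized for. This rests on taking the SD, power and error rate as printed and assuming a two-sided test. With a one-sided test the nearest reading is 9 points, and the factor is still about three.

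The number of patients may well be what the sponsor intended; the stated difference is what is wrong. It must be corrected because it is the trial's only statement of its target effect. It also hides how far power depends on the SD: for 10 points, power runs from 91% to 46% across the quoted range.

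**What to change.** - Check the original calculation for the control mean, target difference, SD and sidedness, and print all four.
- Assuming that check confirms it, restate the target as a mean difference of 10 CCI points (for example 30 versus 20) with SD 20, two-sided 5%, and say that 126 evaluable patients give about 80% power for that difference.
- Make the clinical relevance statement refer to the same figure. The sponsor should stand behind 10 points as relevant, since the article currently offers no support for that value.
- Add the power for 10 points across the quoted SD range: 91% (SD 17), 80% (SD 20), 61% (SD 25) and 46% (SD 30).

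Cost: a corrected sentence and one added line in the article and the full protocol, and in the registry entry if it carries the same figure (not seen here). The correction itself needs no extra patients. Recruitment is planned to run until September 2027, so it can be made before results are known. The interim power statement and the dropout inflation should be rechecked against the corrected target at the same time.

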**Methods:**

This is a multicenter, international, randomized controlled trial. Eligible participants include adults scheduled for elective open AAA surgery. A total of 152 participants will be randomized 1:1 to receive either standard preoperative care or a 6-week multimodal prehabilitation program consisting of supervised exercise training, individualized nutritional support, and psychological counseling. The primary outcome is the rate of postoperative complications as measured by the Comprehensive Complication Index (CCI). Secondary outcomes include length of hospital stay, and readmission rates, changes in functional capacity, health-related quality of life and anxiety & depression. Data will be analyzed on an intention-to-treat basis. The study complies with SPIRIT 2013 guidelines and is registered at ClinicalTrials.gov (NCT05756283).

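### The total of 152 was obtained by multiplying 126 by 1.2, so it covers a dropout of about 17%, not the stated 20%; the effect is minor

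*Protocol article*

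**What the plan says.** Section 3.6.1 (Sample size) of the protocol article builds the total in two steps. The first gives the number needed before losses: "Given the inputs, we require a total of 126 patients to achieve standard 80% statistical power and 5% tolerance". The second adds the allowance for losses: "After considering a 20% dropout rate, we require 152 patients (76 per group) in this study". The article does not say how the allowance was calculated and does not define dropout. The Methods part of the abstract carries the same total forward: "A total of 152 participants will be randomized 1:1".

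The inputs given for the first step are "We have chosen 30 as the most clinically relevant mean difference for the CCI and standard deviation of 20", set against literature values described as "the mean CCI ranges from 25–35 after open AAA repair, and their standard deviations are 17–30". They matter here only because any statement about power depends on them.

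**The concern.** A dropout rate is ordinarily a share of the patients who enter the trial. If a fraction d of those randomised is lost and n must remain, n/(1 - d) must be randomised. Multiplying by (1 + d) always gives a smaller number, and the shortfall grows with d. The stated total looks like the product of that multiplication. If so, the three figures in the section (126 needed, 20% lost, 152 randomised) cannot all hold, and the claim of 80% power at the planned dropout is slightly too favourable. A reader of the trial report could show this with one division.

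**Working it through.** **Inputs from section 3.6.1:** 126 required in total (63 per group), 20% dropout, 152 randomised (76 per group), 80% power, 5% error level. Sidedness is not stated; two-sided is assumed below.

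**1. Reproducing the plan's figure.**
- n x (1 + d): 126 x 1.2 = 151.2, rounded up to 152. Per group, 63 x 1.2 = 75.6, rounded up to 76. Both match the plan exactly.
- n/(1 - d): 126/0.8 = 157.5, rounded up to 158. Per group, 63/0.8 = 78.75, rounded up to 79. Neither matches.

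**2. What 152 delivers at 20% dropout.**
- 152 x 0.8 = 121.6, so 121 or 122 patients (60.8 per group on average).
- Shortfall against 126: 4 to 5 patients.
- Check of the alternative: 158 x 0.8 = 126.4, which keeps the 126.

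**3. The dropout that 152 does cover.** (152 - 126)/152 = 26/152 = 17.1%.

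Steps 1 to 3 use only figures printed in the section and do not depend on the effect size.

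**4. Effect on power.** This step needs the difference behind the 126.
- Normal approximation, per group: n = 2 (1.960 + 0.842)² (SD/difference)².
- With the stated difference of 30 and SD 20: 2 x 7.85 x (20/30)² = 6.98, so 7 per group and 14 in total. Across the cited SDs of 17 to 30 the total runs from 12 to 32. None of these is 126.
- With a difference of 10 and SD 20: 2 x 7.85 x (20/10)² = 62.8, so 63 per group and 126 in total. This matches exactly, but a 10-point difference is stated nowhere in the article. It is an inference.

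Power under that inferred difference (10 points, SD 20, two-sided 5%):

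| Evaluable per group | Normal approximation | t test |
|---|---|---|
| 63 (the required 126) | 80.1% | 79.5% |
| 60.8 (152 less 20%) | 78.7% | 78.1% |
| Loss | 1.4 points | 1.4 points |

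The comparison has to stay within one method. Setting the t-test 78.1% against the nominal 80% would overstate the loss, because the t test gives only 79.5% at 126 to begin with.

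At the other end of the range, with the stated difference of 30, power at 60.8 per group is above 99.9% for an SD of 20 or of 30.

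**The case against.** Four points can be made for the plan as written.

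- *Multiplying by 1.2 is a common shortcut, and 20% might mean 20% of completers.* On that reading 152 would be right. The section speaks of a dropout rate, however, and gives no such definition, so this does not rescue the sentence.
- *The analysis is by intention to treat with all randomised participants (section 3.1), and complications are recorded during the admission (section 3.5.6).* Someone who stops the programme or misses the later visit may therefore still have a Comprehensive Complication Index score. This stands in part. Dropout in section 3.6.1 need not mean a missing primary outcome, and the real loss of information may be smaller than 20%. It does not repair the allowance, which the section itself sets at 20%.
- *The power figures depend on a difference that the article does not state.* This stands fully. A reader might infer that the trial has 78% power, or that it is underpowered. The document does not support either statement: on its literal inputs the power would be close to 100%, and the 78 to 79% appears only if a 10-point difference is assumed.
- *The consequence is small.* This also stands. Four to five evaluable patients and about 1.4 points of power are minor beside the cited SD range of 17 to 30, and beside the mismatch between a difference of 30 and a total of 126 in the same section.

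**Conclusion.** The dropout allowance is wrong as written. On the section's own figures, 152 randomised patients less 20% leaves about 121, not 126, and 152 protects the 126 only up to a dropout of 17.1%. A full 20% allowance would be 158, six more. This conclusion rests only on reading the dropout rate as a share of those randomised.

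The size is minor. A loss of about 1.4 points of power (80.1% to 78.7% by normal approximation, 79.5% to 78.1% by t test) assumes a difference of 10 points, SD 20 and a two-sided 5% level. The 10 points are inferred because they reproduce the 126; the article gives 30. The power loss is therefore conditional, whereas the shortfall in patients is not. Nothing here shows that the trial must recruit more patients or that 20% of participants will lack a primary outcome.

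**What to change.** Keep 152 and correct the sentence in section 3.6.1 in one of two ways:

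- state that 152 randomised patients allow for a dropout of about 17% while keeping the required 126; or
- keep 20% and state that about 121 patients would then remain, with power slightly below 80%.

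Do not add a numerical power figure until the sponsor has reconciled the stated difference of 30 with the 126. A sentence quoting power for 10 points beside one giving the difference as 30 would introduce a new contradiction. It would also help to say whether dropout means a missing primary outcome.

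The cost is one sentence. The abstract's total, the recruitment target and the analysis do not change; the stated dropout allowance or power becomes slightly less favourable. The separate mismatch between 30 and 126 needs its own correction and is best handled in the same edit.
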